## Materials and methods

### Objectives and hypotheses

We will test the feasibility and efficacy of a newly developed personalized intervention focused on replacing sedentary time with light-intensity physical activity in patients with rheumatoid arthritis. A multitude of techniques will be applied to evaluate the effects of the intervention on several outcomes, including sedentary time (primary outcome), physical activity levels, clinical parameters, cardiometabolic risk factors, and health-related quality of life. In addition, molecular analyses will be conducted in skeletal muscle and blood samples to gather knowledge on the potential underlying mechanisms by using targeted and non-targeted omic approaches. Finally, responders and non-responders (based on the reduction of sedentary time) will be compared to test the efficacy of reducing sedentary behavior on health-related outcomes in rheumatoid arthritis.

Our two main hypotheses are that (1) the intervention will be effective in reducing sedentary time, and (2) reducing sedentary time will improve clinical parameters, cardiometabolic risk factors, and health-related quality of life.

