### Experimental design

We will conduct a 4-month, parallel-group, randomized controlled trial, in which patients will be assessed at baseline (PRE) and after 4 months (POST) for sedentary behavior (primary outcome) and physical activity levels; clinical parameters; anthropometric parameters and body composition; aerobic fitness; muscle function; blood pressure; cardiovascular autonomic function; vascular function and structure; health-related quality of life; blood samples and oral glucose tolerance test; immune function; muscle biopsy; and food intake. Sedentary behavior and physical activity levels will be also evaluated at the second month to check adherence to the intervention.

After baseline assessments, patients will be randomly allocated to either a control or intervention group using a simple randomization (1:1 ratio) procedure, by computer-generated random numbers in SAS 9.3 (SAS Institute Inc., Cary, NC, USA) for Windows. An external researcher will generate the allocation sequence and be contacted after patients’ enrollment. All assessors will be blinded to patients’ allocation and will be responsible for patients’ recruitment and enrollment. However, a trained researcher who will not be blinded to patients’ allocation will be responsible for assigning patients, and for applying and monitoring the Take a STAND for Health intervention. The control group will receive standard care, including general advice on healthy lifestyle. The intervention group will receive standard care supplemented with a specific personalized intervention aimed at reducing sedentary time (called Take a STAND for Health), which will not require alteration to usual care pathways (including use of any medication). In brief, this intervention comprises individually tailored progressive goals aimed at reducing sedentary time, which will be selected with the active participation of the patient. A trained researcher will assess adherence to the goals via phone calls and personal interviews throughout the follow up.

The current study is registered in an international database of clinical research studies (clinicaltrials.gov, NCT03186924). This manuscript is described according to the Standard Protocol Items: Recommendations for Interventional Trials (SPIRIT) checklist (Fig. 1, Additional file 1) and the findings from this study will be reported according to the recommendations of the Consolidated Standards of Reporting Trials (CONSORT) guidelines (Fig. 2).

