#### Clinical assessment

Disease activity will be assessed by the Disease Activity Score in 28 joints [37], which is based on the number of tender and swollen joints, C-reactive protein or erythrocyte sedimentation rate, and the patient’s general health status. Higher scores represent more severe disease activity. The Health Assessment Questionnaire [38], which evaluates physical functioning in eight domains of daily life, will also be used; higher scores represent greater disability. Disease duration, current dose of prednisone, current use of biological agents (e.g., anti-TNF, anti-IL6, anti-IL1, B cell depleting-agents, and T cell activation-inhibiters), non-biological disease-modifying anti-rheumatic drugs (e.g., methotrexate, leflunomide, and hydroxychloroquine), and other medications will be obtained by reviewing medical records and interviewing patients. Pain will be assessed using a visual analogic scale [39], in which patients grade their pain using a 10-point scale; 0 means no pain and 10 means severe or unbearable pain. Fatigue will be assessed by the Fatigue Severity Scale [40] in which lower scores indicate lower fatigue.

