#### Anthropometry and body composition

Height will be measured by a wall-mounted stadiometer. Body mass will be measured by a digital scale, with a sensitivity of 100 g. BMI will be calculated using the following equation: body mass (kg)/height (m)^2^. Waist circumference will be measured using a plastic tape measure placed around the smallest circumference between the lowest margin of the ribs and the upper margin of the iliac crest, with subjects standing. Body composition (i.e., bone, lean and fat mass, and visceral adipose tissue) will be measured by dual-energy x-ray absorptiometry (DXA), using a Lunar iDXA densitometer (GE Healthcare, WI, USA). All assessments will be performed by the same trained technician.

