### Statistical analysis

Data normality will be tested using the Kolmogorov-Smirnov or the Shapiro-Wilk *W* test. Parametric data will be presented as mean ± 95% CI. Non-parametric data will be log-transformed and presented as back-transformed mean ± 95% CI. The ES (Cohen’s *d*) will be calculated and interpreted as small (0.2–0.4), medium (0.5–0.7), or large (≥ 0.8).

Generalized linear mixed model analyses will be performed for each dependent variable, with group and time as fixed factors and patients as a random factor; the models will be adjusted by age, BMI, disease activity, and if different between groups, baseline values of the outcome variable. In the case of significant *F* values, a post-hoc test with Tukey’s adjustment for multiple comparisons will be performed. Analyses will be conducted according to the intention-to-treat principle, in which missing values will be handled by the generalized linear mixed model by using maximum likelihood to estimate the parameters of the model. To test the influence of reducing sedentary time on health-related outcomes, patients will be allocated into “responder” and “non-responder” sub-groups (according to changes in sedentary time); thereafter, the dependent variables will be compared between them.

Data analysis will be performed using the SAS 9.3 (SAS Institute Inc., Cary, NC, USA) for Windows. The level of significance will be set at *p* ≤ 0.050.

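### The fixed covariate set (age, BMI, disease activity) is applied to every model, including those in which BMI or DAS28 is the outcome, where the rule does not work as written

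*Protocol article*

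**What the plan says.** All of this is in the protocol article.

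- Statistical analysis, scope: "Generalized linear mixed model analyses will be performed for each dependent variable". Group and time are fixed factors and patient is random, so the PRE and POST values are both response rows.
- Statistical analysis, covariates: the fixed set is given by "the models will be adjusted by age, BMI, disease activity", and the full clause reads "the models will be adjusted by age, BMI, disease activity, and if different between groups, baseline values of the outcome variable". The word baseline is attached only to the outcome variable. No exception is written for any outcome.
- Statistical analysis, follow-up tests: after a significant F, pairwise comparisons are made with Tukey's adjustment. Missing data are handled by maximum likelihood.
- Experimental design: the families assessed at PRE and at 4 months (POST) include "clinical parameters; anthropometric parameters and body composition".
- Clinical assessment: "Disease activity will be assessed by the Disease Activity Score in 28 joints".
- Anthropometry and body composition: "BMI will be calculated using the following equation", so BMI belongs to the anthropometric outcomes.
- Objectives and hypotheses, second main hypothesis: "reducing sedentary time will improve clinical parameters, cardiometabolic risk factors, and health-related quality of life".

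**The concern.** Two of the three fixed covariates are also outcomes, and one of them, DAS28, is among the clinical parameters that the second main hypothesis expects to improve. This raises two separate questions.

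1. What happens in the DAS28 and BMI models, where the outcome also stands on the right-hand side?
2. What happens in the other models if the covariate is the value at the current visit? The model would then condition on something that the intervention may change, and the part of the effect that runs through it would be removed.

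At stake are the standard errors and p-values for DAS28 and BMI and, under one reading only, the effect estimates for the remaining outcomes.

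**Working it through.** The plan gives no figure for this point, so there is none to reproduce. The check takes the two possible readings in turn. Correlations and effect sizes are assumptions, since the article gives none. I also assume that the model contains a group-by-time term, which a two-visit parallel-group comparison needs.

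**Reading A: values at the current visit**

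*Own models.* The covariate equals the response in every row. A fit to simulated data gives a coefficient of 1 for the covariate and 0 for group, time and group-by-time. The model says nothing about treatment.

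*Other models.* Illustration with 15 per arm. The intervention changes the covariate by -0.50. The outcome change is 0.5 × (covariate change) - 0.25 × group + noise with SD 0.6.

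- Total effect: 0.5 × (-0.50) - 0.25 = -0.50.
- Adjusted for the covariate's change: estimate about -0.25, power about 18%.
- Adjusted for its PRE value: estimate about -0.50, power about 46%.

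**Reading B: PRE values**

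*Other models.* As the last line shows, the full effect is recovered. There is no mediator problem.

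*Own models.* Take unit variance at both visits and PRE-POST correlation ρ, with no treatment effect. PRE rows have true slope 1 on the PRE covariate and POST rows have slope ρ. One common slope must serve both, and it settles at b = (1 + ρ)/2. Then:

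- PRE residual variance = (1 - b)²
- POST residual variance = (ρ - b)² + 1 - ρ²
- The residuals at the two visits are negatively correlated, so the patient variance is estimated at zero and the model uses the pooled variance s², the mean of the two.
- Ratio of model SE to true SE for the POST contrast = √(s² / POST residual variance)
- The same ratio for group-by-time = √(2s² / [2(1 - ρ)]) = √((3 + ρ)/4)
- Large-sample type I error = 2 × [1 - Φ(1.96 × ratio)]

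| ρ | b | PRE var. | POST var. | s² | POST SE ratio | POST error | Group-by-time SE ratio | Group-by-time error |
|---|---|---|---|---|---|---|---|---|
| 0.3 | 0.65 | 0.1225 | 1.0325 | 0.5775 | 0.748 | 14.3% | 0.908 | 7.5% |
| 0.5 | 0.75 | 0.0625 | 0.8125 | 0.4375 | 0.734 | 15.0% | 0.935 | 6.7% |
| 0.7 | 0.85 | 0.0225 | 0.5325 | 0.2775 | 0.722 | 15.7% | 0.962 | 5.9% |

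The group-by-time ratio tends to 1 as ρ tends to 1, so that test is least affected for a very stable measure.

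Simulated null trials at the planned size (24 and 30 patients, random intercept, three covariates, ρ from 0.3 to 0.7) agree:

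| Test, nominal 5% | Self-covariate, REML | Self-covariate, ML | Self-covariate dropped |
|---|---|---|---|
| Group-by-time | about 6-8% | 8-9% | 5-7% |
| POST contrast, unadjusted and ungated | 12-15% | 15-17% | 4-8% |
| POST contrast, significant group-by-time F, then Tukey over four cells | 3.5-4.5% | 4.3-6.1% | not needed here |

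The point estimate is not biased. In one simulated data set the group-by-time estimate was -0.818 with and without the PRE covariate, while its SE fell from 0.318 to 0.293 and the patient variance went to zero.

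**The case against.** **Timing is a detail for the analysis plan.** Naming age, BMI and disease activity as adjustment factors ordinarily means baseline characteristics, and a condensed article may leave the visit to a fuller document. This stands as far as the visit goes. It does not rescue the rule for DAS28 and BMI, because the article itself applies one covariate set to every outcome and the PRE reading also misfires there.

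**With PRE values this is ordinary baseline adjustment.** That would be true if POST were the only response. The planned model has time as a fixed factor and patient as random, so PRE is a response row as well. An unchanged point estimate does not show that the standard error is right.

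**Stronger readings that a reader might infer, and why the documents do not support them:**

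- *The DAS28 and BMI tests are invalid on either reading.* With PRE values the estimate is unbiased and the group-by-time test is only mildly anti-conservative. Part of the ML excess is ordinary small-sample behaviour, since rates of up to about 7% remain once the self-covariate is dropped.
- *The false-positive rate for these outcomes is 12-17%.* That is the rate of an unadjusted, ungated POST contrast. The article plans Tukey comparisons only after a significant F, and that sequence stays near 5%.
- *All outcomes are adjusted for a mediator.* The article nowhere says that POST values of the covariates will be used. The halved effect in the illustration depends on that reading and on assumed effects.
- *The primary outcome is compromised.* Sedentary time is not one of the covariates. With PRE values it is untouched.

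**Conclusion.** The point holds in a limited form. One covariate rule is written for all outcomes, and it does not work for the two outcomes that are also covariates. With current values the DAS28 and BMI models are degenerate. With PRE values, the more natural reading, their standard errors are too short: by about 4-9% for group-by-time (ratios 0.962 to 0.908) and about 25-28% for the POST contrast (ratios 0.748 to 0.722) in the large-sample calculation. This puts the group-by-time type I error at about 6-8% with REML and 8-9% with ML, and the planned gated Tukey sequence near 5%. These figures assume a PRE-POST correlation of 0.3 to 0.7, 24 to 30 patients, a random-intercept model and a group-by-time term.

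The mediator concern is conditional on current values being entered and disappears with PRE values, as does any effect on the primary outcome. The matter is a correction to the analysis of secondary outcomes, of which DAS28 is the more important because it falls under the second main hypothesis.

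**What to change.** Two sentences in the analysis section:

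1. Age, BMI and disease activity enter all models as PRE values only.
2. In the DAS28 and BMI models, either the self-covariate is dropped while PRE stays a response row, or POST is the only response with PRE as covariate.

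Both are needed: the first alone leaves PRE on both sides of the DAS28 and BMI models. Either option in the second is sound. In simulation with 15 per arm and an assumed effect of -0.80, the POST-only model gave a mean estimate of -0.79 with an empirical SE of 0.257, against 0.274 for change scores. It would also help to say how closely related outcomes (body mass, C-reactive protein, erythrocyte sedimentation rate) are handled. The cost is wording only, with no new data.

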#### Sample size

Sample size calculations were performed using G-Power® software, v. 3.1 (Universität Düsseldorf, Düsseldorf, Germany), based on the study by Lewis et al. that reported the effects of reducing sedentary behavior in an elderly population (i.e., a reduction of 52 min in total sitting time) [33]. According to the estimation, 24 patients (12 per arm) are required to achieve 95% power (α), with a significance level of 5% (β), and assuming an effect size of 0.58 for the primary outcome (i.e., sedentary time). Estimating a dropout rate of ~ 25%, at least 30 patients will be recruited. Considering that this sample size could be underpowered for some secondary outcomes, we will try to increase this estimated sample based on the feasibilities of our laboratory (including funding, capacity of research staff and facilities, and available patients), in line with contemporary recommendations [34, 35].

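### The responder versus non-responder comparison is worded as a test of efficacy, but it splits patients on post-randomisation behaviour and can support only an exploratory association

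*Protocol article*

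**What the plan says.** Under Objectives and hypotheses, the protocol article's second main hypothesis is that "reducing sedentary time will improve clinical parameters, cardiometabolic risk factors, and health-related quality of life". The same section says that responders and non-responders, defined by their reduction in sedentary time, "will be compared to test the efficacy of reducing sedentary behavior on health-related outcomes in rheumatoid arthritis".

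The Statistical analysis section plans two things for the health outcomes.

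- **By randomised arm, on the intention-to-treat principle:** "Generalized linear mixed model analyses will be performed for each dependent variable, with group and time as fixed factors and patients as a random factor". On covariates, "the models will be adjusted by age, BMI, disease activity, and if different between groups, baseline values of the outcome variable".
- **By observed behaviour:** patients are classed as responders or non-responders, with the declared purpose of testing whether sitting less affects health. The plan's words for the split and its use are "sub-groups (according to changes in sedentary time); thereafter, the dependent variables will be compared between them".

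Neither section describes the second comparison as exploratory or associational.

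**The concern.** Randomisation makes the arms comparable. It does not make patients who ended up sitting less comparable with those who did not. Change in sedentary time is measured from baseline to month 4, and so are the outcomes it is meant to explain.

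The article itself points to plausible common causes. The Introduction notes that disability and active disease can limit activity (it says this of moderate-to-vigorous activity). Disease activity, disability, pain and fatigue are also listed outcomes under Clinical assessment. A patient whose symptoms ease may sit less and also score better, without the first causing the second.

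If the arms are pooled, arm is a further common cause. The intervention group receives five individual sessions and weekly calls or messages, which the control group is not described as receiving. That contact could affect self-reported outcomes directly.

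What is at stake is the conclusion. If the randomised comparison shows nothing and the responder comparison is significant, the present wording would allow the second result to be reported as evidence of efficacy.

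**Working it through.** **The plan's own figure.** The article gives no figure for the responder comparison, so there is none to reproduce. The sample size is used below only as an input.

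**Inputs from the article**
- 24 patients, 12 per arm, after dropout; 30 recruited, so 15 per arm if nobody is lost (Sample size).
- Effect size 0.58 on sedentary time (Sample size). I take it as a shift of 0.58 SD in change in sedentary time between arms; the article does not say which effect-size metric it is.
- Significance level: "The level of significance will be set at *p* ≤ 0.050", taken as two-sided.

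**Assumptions**
- The within-arm correlation r between less sitting and a better outcome arises entirely from a shared cause. The article gives no value, so r runs from 0 to 0.5.
- Sedentary time has no effect on the outcome, and neither does arm.
- Responders are split at the median change, with both arms pooled.

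**Model.** With g = 1 for the intervention arm, u the shared cause, and u, e₁, e₂ independent standard normal:

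- change in sitting = −0.58·g − √r·u + √(1−r)·e₁
- change in outcome = √r·u + √(1−r)·e₂

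A t test then compares the outcome between responders and non-responders, and separately between arms (8,000 to 10,000 runs per setting).

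| r | Responder split, 12 per arm | Responder split, 15 per arm | Randomised arms |
|---|---|---|---|
| 0 | about 5% | about 5% | about 5% |
| 0.1 | 6–7% | 7% | about 5% |
| 0.3 | 18–19% | 23% | about 5% |
| 0.5 | 46–48% | 56% | about 5% |

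Across all settings the randomised comparison lay between 4.6% and 5.6%.

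**Hand check at r = 0.3, 12 per half.**
1. The arm shift dilutes the pooled correlation to 0.3/√(1 + 0.58²/4) = 0.3/1.041 = 0.288.
2. A median split gives an expected difference of 2 × 0.798 × 0.288 = 0.46 SD, where 0.798 = √(2/π).
3. The within-half SD is √(1 − (0.798 × 0.288)²) = 0.973, so the standardised difference is about 0.47.
4. The noncentrality is 0.47 × √(12/2) = 1.16. On 22 degrees of freedom this is significant in about 20% of trials.

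The same steps at r = 0.5 give a standardised difference of 0.83, noncentrality 2.03 and about 49%. This large-sample approximation runs slightly above the simulation, as expected.

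**Variations**
- *Cut at zero change instead of the median:* no material difference.
- *Adjusting for a baseline covariate correlated 0.3 with the shared cause:* 16% at r = 0.3 and 40% at r = 0.5 with 12 per arm; 20% and 49% with 15 per arm.
- *Intervention arm only:* 12% and 24% with 12 patients; 14% and 32% with 15.
- *Continuous change in sedentary time, adjusted for arm and baseline covariates, 12 per arm:* 26% at r = 0.3 and 65–67% at r = 0.5. These exceed the rates for the split because the continuous measure detects the confounded association more efficiently.

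**The case against.** The strongest reply is that the valid analysis is already planned. Every dependent variable has an intention-to-treat comparison by randomised group, and the objectives mention the responder comparison last. This stands, and it limits the point. A reader might infer that hypothesis 2 rests on the responder split alone; the documents do not support that. The fault is that an additional, non-randomised comparison is described as an efficacy test.

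The correlations are assumed, and at 0.1 the inflation is slight. This also stands. It would be too strong to say that any common cause yields false positives: the error rate is inflated by an amount that depends on an unknown correlation.

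The plan limits confounding by adjusting its mixed models for age, BMI and disease activity and by excluding patients on unstable drug therapy. This helps in part. Even if the same covariates are carried into the responder comparison, baseline values cannot account for causes that arise during follow-up, and stable medication does not prevent symptoms from fluctuating.

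Three further criticisms are tempting but should not be made.
- The absence of a responder cut-off is not a finding, because an article commonly leaves this to the full protocol or analysis plan.
- Regression to the mean in baseline sitting is not shown to create a difference. Measurement error there would tend to dilute one, unless the outcome shares that error.
- The Discussion says the results could inform prescriptions; it does not make that the aim of this comparison.

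**Conclusion.** The point holds in this limited form and is wrong as written. The article assigns an efficacy question to a comparison that randomisation does not protect. Whatever cut-off or covariates a fuller document adds, they would not turn it into a test of efficacy.

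With 12 per arm and no true effect, the false-positive rate per outcome is about 18–19% at an assumed correlation of 0.3 and 46–48% at 0.5, against about 5% for the arms. These sizes rest on the assumed correlations, a pooled split and 0.58 read as an SD shift. Restricting the split to the intervention arm roughly halves the rate at 0.5 but still leaves it well above 5%. The direction of the problem does not depend on any one of these choices. The randomised analysis of the health outcomes is unaffected.

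**What to change.** 1. State that hypothesis 2 is tested by the already planned intention-to-treat comparison of the health outcomes between randomised arms. Add that this estimates the effect of assignment to the intervention.
2. In Objectives and hypotheses and in Statistical analysis, replace the wording that presents the responder comparison as a test of efficacy or influence. Say instead that it is an exploratory description of how change in sedentary time is associated with the outcomes.
3. State that no efficacy conclusion will be drawn from it, whatever its p value.
4. If change in sedentary time is modelled as a continuous variable, give that model the same label. It gains precision but does not remove the confounding.

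I would not offer arm as an instrument for change in sedentary time as a simple remedy. The extra sessions and calls may affect outcomes by routes other than sitting, which would break the assumption that method needs.

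The cost is a few sentences, with no new data or analyses. The sponsor gives up a causal claim from the responder analysis that the data cannot support.
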